#### Econosmic analysis

The economic analyses will include program cost measures, health resource use and cost, and patient quality of life. The cost-effectiveness/utility analysis will be conducted from the Ontario government healthcare system perspective.

#### Implementation processes

For quantitative indicators (volunteer self-efficacy, completeness of the TAP-App, PHR uptake, and the ORCA), a paired *t* test will be conducted to examine the mean differences between relevant time points. A descriptive method [69] will be used to explore implementation questions collected via qualitative methods. An inductive and deductive analysis approach will be used. Using NVivo 10 software, open coding will be used to capture participants’ perspectives of implementation and to track the process of implementation from field notes. These codes will be collapsed under pattern codes [70] which will be organized under normalization process theory constructs to track factors influencing implementation. An initial code book will be derived from the first two to three discussion groups and revised as needed to capture emerging themes. Two research team members will review all transcripts and notes pages and develop a codebook to capture emerging themes. Analysis will focus on implementation and understanding how each key group fits within Health TAPESTRY as well as their needs within the intervention. NVivo 10 matrix queries will be used to examine differences and similarities in perceptions based on of each group (healthcare provider, volunteer, and client). Data collection will take place concurrently with data analysis, so as to ensure that new themes are fully explored.

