### Intervention

A visual depiction of the study flow and planned timeline is provided in Additional file 2. A detailed description of the intervention is provided in Additional file 3. A screenshot of the virtual learning centre and training modules are shown in Additional File 4. A brief summary of the intervention has been described and is visually depicted in Fig. 2. A client (the research participant) will receive a visit in their home from a pair of trained volunteers. The volunteer pair will collect information electronically using a tablet computer which houses a specifically designed Health TAPESTRY software application (TAP-App). Information such as life and health goals, daily life activities, and general health will be collected using structured surveys and unstructured narratives (see Additional file 3). The information gathered will be organized in a report summarizing any alerts, key issues, observations, and goals. This report will be securely sent electronically to an intake team at the clinic. Intake teams may include any combination of healthcare professionals and were put in place to address high-health-need patients including high users of the healthcare system and Health TAPESTRY clients.

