Demographic information including age, gender, level of education, marital status, ethnicity, language spoken, and number of medications, falls, adverse events, and economic analysis not included in the above table

*T*
_*0*_ baseline, *T*
_*3*_ 3-month collection, *T*
_*6*_ 6-month collection, *T*
_*12*_ 12-month collection

^a^Analyses will be adjusted for participant gender and MFHT site (McMaster Family Practice or Stonechurch Family Health Centre)

**Table 3 Tab3:** Summary of trial client outcomes and implementation processes

Implementation processes			
Variable/outcome	Outcome measure	Timing	Methods of analysis
Volunteer self-efficacy	3-item self-efficacy rating of communication with client, performance of tasks necessary for home visit (i.e., navigate TAP-App) and handling unexpected issues (0–100 % scale)	Prior to each home visit	Mean differences for the first 3 months of visits compared to the second 3 months of visits
Completeness of TAP-App used by volunteers	Time to complete each module; number of items missed	*T* _6_, *T* _12_	Mean differences where applicable
Client satisfaction with volunteers	Description of experience with volunteer home visits	*T* _3_, *T* _12_	Qualitative descriptive method
Uptake of personal health record by clients	PHR metrics including number of times logged in, features used, number of secure messages sent, issues encountered, and described experience with the personal health record	*T* _0_, *T* _6_, *T* _12_	Mean differences where applicable; content analysis with frequency counts of each category where applicable
Type and extent of healthcare team involvement with client	Chart audit to track actions of healthcare team (type of follow-up, team members involved)	*T* _6_	Content analysis with frequency counts of each category of resource
Quality and extent of healthcare team functioning and organizational readiness for change by health team members	Described in qualitative interviews	*T* _3_, *T* _12_	Qualitative descriptive method
	ORCA [66]		Mean difference between *T* _3_ and *T* _12_
How often and what types of community resources are utilized by clients?	Chart audit to track connections to community resources and programs	*T* _6_	Content analysis with frequency counts of each category of resource
Type and extent of involvement of clients in program	Described in qualitative interviews	*T* _6_	Qualitative descriptive method

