To compliment the qualitative data collected and to further understand the implementation of the intervention and the readiness of healthcare team members for change, quantitative data will also be collected. Organizational readiness of members across MFHT will be measured using the Organizational Readiness for Change Assessment (ORCA) [65]. Time between volunteer completion of data collection, report placement into the EMR, and discussion by intake team will also be recorded and tracked across the trial. The follow-up actions of the healthcare team will be described via chart audit of the EMR. Action type including communication method and the actions made by the healthcare team will be examined. Types of community resources recommended and utilized by participants will also be recorded. Finally, the types of life and health goals generated by participants and the proportion of recommendations made or actions taken to address these goals will be recorded. Other implementation elements complimented by a quantitative measure are volunteers’ self-efficacy to fulfill their role as a volunteer, the completeness of the initial assessments completed by the volunteers during home visits, and PHR uptake and use (see Tables 2 and 3 for descriptions).

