Interventions and expertise	Experimental intervention-flexibility	TAP-reports reviewed and action plan is developed for that particular person based on their individual self-report information so action plans are all different. There is not a “one size fits all” approach to reports. No specific instructionsgiven to intake teams on process, allowed teams to develop own process and workflow for TAPESTRY; practice was allowed to be different between the two clinics. Never forced clients to use PHR to facilitate connection to healthcare team. At least one home visit by the volunteer was initiated, but no minimum or maximum follow-up visits were enforced in the trial	5
	Experimental intervention-practitioner expertise	MFHT and intake teams made up of different people, intake teams changed throughout the trial, elements of care plan carried out by various MFHT members, regardless of level of expertise	5
	Comparison intervention-flexibility	Control individuals allowed to receive any type of care from any healthcare professional at the clinic. Individuals in the control group do not receive volunteer visits, the TAP-App and are not discussed at the intake team meetings	5
	Comparison intervention-practitioner expertise	Same MFHT members are involved in the care of individuals in the intervention and control groups	5
Follow-up and outcomes	Follow-up intensity	Formal follow-up to collect research outcomes (baseline, 6 and 12 months). No formal volunteer home visit follow-up schedule of clients, no instruction for MFHT of clinic follow-up	4
	Primary trial outcome	Primary out is GAS score, which is subjective, person-centered care outcome and clinically meaningful to client	5
Compliance/adherence	Participant compliance with “prescribed” intervention	No formal strategy to encourage compliance; methods to encourage use of PHR, improve volunteer confidence in role	5
	Practitioner adherence to study protocol	Only subtle strategies to encourage intervention to move forward have left for organic process, but no formal strategy to monitor adherence or encourage adherence; researchers sat in intake team meetings early on to track development of processes, however, have withdrawn researchers have intake teams to lessen influence of initiative	4
	Analysis of primary outcome	Using intention to treat principle, intention to include all experiences in evaluation (good and bad), statistical analysis plan will work under “noise”	5

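### One paired t test is stated for four implementation measures; as described it suits only personal health record uptake without further steps

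*Protocol article*

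**What the plan says.** The test is set out in the Implementation processes part of Data analysis. It opens "For quantitative indicators (volunteer self-efficacy, completeness of the TAP-App, PHR uptake, and the ORCA), a paired" t test, and goes on to say that this test "will be conducted to examine the mean differences between relevant time points". It does not name the unit to be paired.

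Other parts of the article describe how the four measures arise:

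- **Volunteer self-efficacy.** Table 3 gives the timing as "Prior to each home visit" and the analysis as "Mean differences for the first 3 months of visits compared to the second 3 months of visits". Table 4 adds that, beyond one initiated visit, "no minimum or maximum follow-up visits were enforced in the trial".
- **TAP-App completeness.** Table 3 lists time per module and items missed, at T6 and T12, with mean differences where applicable. The Implementation processes part of Outcomes describes the measure as "the completeness of the initial assessments completed by the volunteers during home visits". Under Design and Control, the control group has no volunteer visits in the first 6 months and is offered the intervention after that.
- **PHR uptake.** Table 3 lists client-level metrics at T0, T6 and T12.
- **ORCA.** Table 3 compares T3 with T12. The Outcomes text says it is measured in members across the McMaster Family Health Team (MFHT). Table 4 notes that "intake teams changed throughout the trial".

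**The concern.** A paired t test needs one value per unit at each of two times. Three of the four measures do not arrive in that form, and each departs from it differently. Self-efficacy gives many ratings per person per block. Initial TAP-App assessments happen once per client, at a time set by the delayed start. ORCA is answered by whichever staff respond at each time.

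Applied as written, the test could therefore do one of three things: treat repeated ratings from one volunteer as independent pairs and understate the error, look for client pairs that the design is not expected to supply, or discard anyone seen at one time only. Evaluating implementation is part of the stated overall aim, and the Discussion relies on it to interpret the comparative results.

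**Working it through.** The article gives no number of volunteers, visits or ORCA respondents and no result for these analyses, so there is no stated figure to reproduce. The check has two parts.

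**1. Does each measure give one pair per unit?**

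| Measure | Natural unit | Values per unit | Pairs as described? |
|---|---|---|---|
| PHR uptake | client | one set at each of T0, T6, T12 | yes |
| Self-efficacy | volunteer | one per visit, visit count open | only after averaging within volunteer and block |
| TAP-App, initial assessments | client | one initial assessment | not by client; possibly by volunteer |
| ORCA | staff member | one at T3, one at T12 if present and responding | only for those who answer twice |

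For TAP-App, the first group has its initial assessments after randomization. The delayed group can have them only after 6 months. The two halves therefore draw largely on different clients.

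**2. What happens to self-efficacy if visits are the pairs?**

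Let each of V volunteers give m ratings per block, paired visit by visit. Let τ² be the variance between volunteers in their true change and σ² the residual variance of one rating.

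- Variance of the mean change assumed by the visit-level test: (τ² + 2σ²)/(Vm)
- True variance: (mτ² + 2σ²)/(Vm)
- Ratio: D = 1 + (m − 1)ρ, with ρ = τ²/(τ² + 2σ²)
- Approximate false-positive rate: 2[1 − Φ(1.96/√D)]

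All inputs are assumptions, with total rating variance scaled to about 1. Setting A has 40 volunteers, half the rating variance between volunteers (σ² = 0.5) and τ² from 0.05 to 0.20. Setting B has 30 volunteers, a between-volunteer share of 0.4 and a volunteer-by-block share v of 0, 0.1 or 0.2, so τ² = 2v and σ² = 0.6 − v.

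Worked example (B, v = 0.1, m = 5): τ² = 0.2, σ² = 0.5, ρ = 0.2/1.2 = 0.167, D = 1 + 4 × 0.167 = 1.67, √D = 1.29, 1.96/1.29 = 1.52, rate 12.9%. The simulation gave 13.1%.

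| Setting | m | D | Formula | Simulated, visits paired |
|---|---|---|---|---|
| A, τ² = 0.05 | 2 / 4 / 8 | 1.05 / 1.14 / 1.33 | 5.6% / 6.7% / 9.0% | about 6% / 7% / 9% |
| A, τ² = 0.20 | 2 / 4 / 8 | 1.17 / 1.50 / 2.17 | 7.0% / 11.0% / 18.3% | about 7% / 11.1% / 17.9% |
| B, v = 0.1 | 2 / 5 / 10 | 1.17 / 1.67 / 2.50 | 7.0% / 12.9% / 21.5% | 7.0% / 13.1% / 21.2% |
| B, v = 0.2 | 5 | 2.33 | 20.0% | 19.7% |
| B, v = 0 | 5 | 1.00 | 5.0% | 4.1% |

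Simulations used 4,000 data sets per setting in A and 3,000 in B, with no true change. With one mean per volunteer per block, the paired t test gave 5.3% and 5.6% in A (τ² = 0.20, m = 4 and 8) and 4.5% to 5.3% across B.

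The inflation thus depends on two things: visits being used as the pairs, and volunteers differing in their change.

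**The case against.** The strongest reply is that the article never says visit ratings will be paired. Comparing two blocks of visits is compatible with one mean per volunteer per block, and the paired t test then holds its level. This stands. A reader might infer that the error bars for self-efficacy are wrong as planned; the documents do not establish that, because the unit is left open. Nor would the estimated change be inflated: the risk is an understated error.

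A reader might also infer that ORCA respondents at T3 and T12 are different people. The documented change concerns intake teams, while ORCA is taken across the MFHT, and staff who answer twice form genuine pairs. What remains is that a paired test drops those who answer once.

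For TAP-App, it is too strong to say that no pairs could exist. Pairing by volunteer is possible, the process is described as iterative, and Table 3 qualifies the analysis as applying where applicable. But repeat visits do not create a second initial assessment for a client, so client pairs are not expected on the article's own wording.

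Finally, an article may leave aggregation and linkage to a fuller plan. That would answer a complaint about missing detail. It does not fully answer this point, because the article does fix a test and applies it to four measures with different structures.

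**Conclusion.** The point holds in limited form. The stated paired t test suits PHR uptake as described. It does not suit the other three measures without a further step: averaging within volunteer for self-efficacy, a different unit or an unpaired comparison for initial TAP-App assessments, and restriction to repeat respondents for ORCA.

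If self-efficacy visits were used as pairs, the false-positive rate would be about 6% to 21% for 2 to 10 ratings per block, under assumed volunteer numbers and variances. There is no inflation if volunteers do not differ in their change. If volunteer means are used, the rate is about 5% and the cost is the loss of volunteers active in one block only. The number of volunteers or ORCA respondents who would be lost cannot be worked out from the article.

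The importance is low. These are implementation measures that complement qualitative work. The primary goal attainment comparison and the sample size are unaffected.

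**What to change.** Replace the single sentence with one analysis per measure:

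- **PHR uptake:** keep the paired approach on the same clients.
- **Volunteer self-efficacy:** linear mixed model with period as fixed effect and a random volunteer intercept and period slope, which also keeps volunteers seen in one block only. The simple version is a paired t test on one mean per volunteer per block, stating that one-block volunteers are excluded.
- **TAP-App completeness (initial assessments):** unpaired comparison of first-group and delayed-group clients that allows for clustering by volunteer or volunteer pair, since each client "will receive a visit in their home from a pair of trained volunteers".
- **ORCA:** mixed model with time as fixed effect and a random respondent intercept, with respondents linked across T3 and T12, so that all answers are used.

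The cost is slightly more analysis work and a change of wording. No new data are needed.

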#### Power and sample size

Assuming baseline scores of 30 on the GAS score in intervention and control groups and a standard deviation of 15 with a power of 80 % and type I error probability of 0.05, we will need to enroll 286 patients overall to detect a mean difference of 5 points on the GAS score representing improvement in the level of goals attained in the intervention group compared with control [71–73]. Previous studies in older adults have demonstrated that this difference indicates a meaningful change in effect and is achievable [71–73]. This sample size will also give sufficient power to detect a difference of 1.0 (SD, 2.5) on the self-efficacy for managing chronic disease scale [54] and a difference of 0.10 (SD, 0.3) on the EQ-5D-5L measure, both identified as meaningful differences. The study will not be powered for planned subgroup analyses, and so these will be considered exploratory. To account for a 10 % potential loss to follow-up in the study, we will aim to enroll 316 participants.

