The analysis will be blind to study group allocation and will follow ITT principle. Dropouts will not be replaced. Reporting will follow the CONSORT extension for pragmatic randomization trials [66] and non-pharmacological interventions [67]. The baseline characteristics of the practices and patients will be reported by group as mean (standard deviation) or median (first quartile, third quartile) for continuous variables, depending on the distribution, and count (percent) for categorical variables. Multiple imputations will be used to handle missing data to enable ITT analysis. The data will be analyzed using generalized estimating equations—assuming exchangeable correlation structure adjusting for baseline scores, to analyze all outcomes [68]. The results will be reported as estimate of the effect, corresponding 95 % confidence interval and associated *p* values. All *p* values will be reported to three decimal places with those less than 0.001 reported as *p* < 0.001. The criterion for statistical significance will be set a priori at alpha = 0.05 and adjusted using the Bonferroni method for multiple secondary analyses. Analyses will be performed using SAS V9.4 (Cary, NC). There will be a single final analysis at the end of the trial. Subgroup analyses will include examining differences between the following groups: men and women; age less than 80 and 80+ years; those residing alone and residing with others; or those with three or more chronic conditions.

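### The secondary power claim for self-efficacy and EQ-5D-5L reproduces at alpha 0.05, but the plan tests secondary outcomes with a Bonferroni adjustment that the claim does not reflect

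*Protocol article*

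**What the plan says.** Under Power and sample size, the protocol article sizes the trial on the goal attainment scaling (GAS) score, for a 5-point difference with "a standard deviation of 15 with a power of 80 % and type I error probability of 0.05", and concludes "we will need to enroll 286 patients overall". It then extends the same number to two further measures: "This sample size will also give sufficient power to detect a difference of 1.0 (SD, 2.5) on the self-efficacy for managing chronic disease scale", and "a difference of 0.10 (SD, 0.3) on the EQ-5D-5L measure, both identified as meaningful differences". No other type I error appears in that section.

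Under Data analysis, Client outcomes, the significance level is 0.05, "adjusted using the Bonferroni method for multiple secondary analyses". The number of tests in that adjustment is not given. The same paragraph says that all outcomes are analysed by generalized estimating equations with adjustment for baseline scores.

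The abstract, Table 2 and the Secondary outcomes section all class self-efficacy and EQ-5D-5L as secondary.

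**The concern.** The power statement and the testing rule use different error rates. The two measures are declared adequately powered at what appears to be 0.05, yet they will be judged at 0.05 divided by the number of secondary tests. Power always falls when alpha is divided, so a claim that only just holds at 0.05 cannot be carried over.

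This matters most for EQ-5D-5L. Its standardized difference (0.10/0.3) equals that of the primary outcome (5/15), so the sample was sized exactly for it at 0.05 and has nothing in reserve. A reader who trusts the statement would expect a real effect of the size the protocol calls meaningful to be detected about four times in five.

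**Working it through.** **Inputs.** From Power and sample size: 286 patients; GAS 5 (SD 15); self-efficacy 1.0 (SD 2.5); EQ-5D-5L 0.10 (SD 0.3). Assumed because not stated: 1:1 allocation (143 per arm) and two-sided tests.

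**Family size k (an assumption).** The protocol does not give k. These counts come from its outcome lists:
- 11: Table 2 rows other than goal attainment.
- 12: hospitalizations and emergency visits counted separately.
- 13: plus the proportion maintaining or improving in the top priority goal area (Primary outcome section).
- 17: admissions and emergency visits each split into the three categories of the Secondary outcomes section (10 other rows + 6 + 1).

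**Formula.** With d = difference/SD and n per arm, power = P(T > t[1 − 0.05/(2k), 2n − 2]), where T is noncentral t with noncentrality d·√(n/2).
- GAS: d = 5/15 = 0.333; noncentrality 0.333 × √71.5 = 2.82.
- Self-efficacy: d = 1.0/2.5 = 0.40; noncentrality 3.38.
- EQ-5D-5L: d = 0.10/0.3 = 0.333; noncentrality 2.82.

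**Step 1: the plan's own figures.** At alpha 0.05, 143 per arm is the smallest arm size giving 80% power for GAS (80.2%), so 286 reproduces. Self-efficacy has 92.1% and EQ-5D-5L 80.2%, so the secondary claim also reproduces at 0.05.

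**Step 2: Bonferroni, no gain from baseline adjustment.**

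| k | alpha | Self-efficacy | EQ-5D-5L |
|---|---|---|---|
| 1 | 0.05 | 92.1% | 80.2% |
| 2 | 0.025 | 87.0% | 71.4% |
| 4 | 0.0125 | 80.7% | 62.0% |
| 5 | 0.01 | 78.4% | 59.0% |
| 11 | 0.00455 | 69.9% | 48.4% |
| 12 | 0.00417 | 68.9% | 47.3% |
| 13 | 0.00385 | 68.0% | 46.3% |
| 17 | 0.00294 | 64.9% | 43.0% |

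For k = 11 to 17, the differences detectable with 80% power are 1.10 to 1.14 on self-efficacy (against 1.0) and 0.131 to 0.136 on EQ-5D-5L (against 0.10).

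**Step 3: baseline adjustment.** If the stated SDs are raw, adjusting for a baseline score with correlation r multiplies the SD by √(1 − r²). At k = 12:

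| r | SD factor | Self-efficacy | EQ-5D-5L |
|---|---|---|---|
| 0 | 1 | 69% | 47% |
| 0.3 | 0.954 | 74% | 53% |
| 0.5 | 0.866 | 84% | 64% |
| 0.7 | 0.714 | 97% | 85% |

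At k = 12, 80% power is reached at r of about 0.42 for self-efficacy and 0.66 for EQ-5D-5L.

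**The case against.** The best defence is the planned model. Both measures are collected at baseline and the analysis adjusts for it, so an unadjusted two-sample calculation may understate power. That stands as a qualification: the Step 2 figures are the no-gain end of a range. It does not rescue the statement as written, because the sample size section gives no correlation and does not say whether its SDs are raw or residual. If they are residual, the gain is already spent.

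A second defence is that the family is undefined and its definition may sit in the SAP. That is fair, and the 65-70% and 43-48% are conditional on the count. The exact count matters little for EQ-5D-5L, which drops below 80% at k = 2 unless baseline adjustment helps.

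A third is that 316 will be enrolled. Even if all 316 were analysed (158 per arm), k = 12 gives 75% and 53%. The number would be smaller if 316 counts both members of couples, since only one of each enters the main analysis.

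Some stronger readings are tempting but not supported:
- That adequate power holds only at unadjusted 0.05 for both measures. Self-efficacy keeps at least 80% up to k = 4.
- That an EQ-5D-5L effect of 0.10 would be missed more often than found. This is true at k = 11 to 17 without baseline gain, but not at k = 12 once r is 0.3.
- That null secondary results will be read as evidence of no effect, or that the economic evaluation depends on the adjusted EQ-5D-5L test. The protocol commits to estimates with 95% confidence intervals, and its Cost-effectiveness section names no such test.

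**Conclusion.** The point stands at moderate severity. The claim of adequate secondary power is correct at alpha 0.05 and does not follow once the protocol's own multiplicity rule is applied. Under 1:1 allocation, two-sided tests, 11 to 17 tests and no baseline gain, power is about 65-70% for self-efficacy and 43-48% for EQ-5D-5L. The case is firm for EQ-5D-5L, which would need a baseline correlation of about 0.66 at k = 12. It is weaker for self-efficacy, where about 0.42 would do.

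This is an inconsistency between two sections, not a miscalculation. A reader might infer that the trial is too small; it is not, for its primary purpose, since the 286 reproduces and the primary test is untouched. Nor is choosing Bonferroni itself an error.

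**What to change.** In Power and sample size, do one of two things. Either give the power for the two measures at the adjusted alpha, stating the number of secondary tests and any baseline correlation assumed, or say that 92% and 80% apply at an unadjusted 0.05.

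In Data analysis, replace Bonferroni by Holm over the same family. Holm controls the same familywise error and rejects everything that Bonferroni rejects, so it is never less powerful. The Bonferroni power is then a lower bound for each outcome.

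The cost is wording in the protocol and the SAP, settled before the comparative analysis. The stated secondary power becomes less favourable. No additional patients are needed, and the primary sample size does not change.
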